### 11.2 Collection of data on adverse reactions

During the course of the study, physicians in charge are to collect data on adverse reactions by the following procedures.

#### Procedure 1:

In interviews with the subjects, encourage them to report spontaneously on any adverse reactions by asking questions (e.g., “Have you had any symptoms that bothered you in the last xx weeks?”).

#### Procedure 2:

Verify if they have had any symptoms through interviews and using checklists. Limit the symptoms to be verified here to the following four symptoms: hypoglycemia, edema, palpitation, and shortness of breath.

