#### 8.3.1 Intensive therapy

The goal for blood pressure control in the intensive therapy arm is defined as "systolic blood pressure < 120 mmHg and diastolic blood pressure < 75 mmHg" as measured on an outpatient basis.

All subjects in the intensive therapy arm are obliged to measure their blood pressure control by using the loaned blood pressure manometer, record and report on the measurement, and the physician in charge is to keep informed of these measurements as a basis for decisions regarding antihypertensive drug dose escalation or replacement. All subjects are to be treated first with predetermined diet and exercise therapy (those already on antihypertensive drugs at study entry are to continue with the medication to achieve their management goal), and if they fail to achieve the blood pressure goal in the first 3 months, they will be given antihypertensive drugs in the following steps to ensure that the blood pressure goal is achieved in 3 to 6 months. However, in those with systolic blood pressure 160 mmHg or greater or diastolic blood pressure 100 mmHg or greater, diet and exercise therapy, where blood pressure control is to be only monitored, is to be skipped, and antihypertensive therapy is to be immediately initiated by following the steps shown below.

In any of the steps described below, diet and exercise therapy is to be continued.

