### 8.3.2 Conventional therapy

The goal for blood pressure control in the conventional therapy arm was defined as "systolic blood pressure < 130 mmHg and diastolic blood pressure < 80 mmHg" as measured on an outpatient basis. The physicians in charge are to choose appropriate therapy for the subjects in the conventional therapy arm in accordance with the Guidelines.

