#### Procedure 3:

Identify symptoms not perceived by the subjects by auscultation and percussion. Additionally, identify changes in the laboratory and vital signs data that may be clinically significant or meaningful. The physician in charge may use his/her judgment in deciding which change (e.g., in laboratory findings) may be construed as “clinically meaningful”.

The physician in charge is to handle symptoms and signs that newly occurred or worsened after the start of the study as adverse reactions, of all symptoms, signs and changes in laboratory findings, and to deal with them appropriately, to follow up on these symptoms and signs until they disappear, resolve or return to their baseline status, and to describe the name(s) of the adverse reaction(s), date of their occurrence, their extent, their causal relationship to the investigational treatment, their severity, and how they were dealt with (e.g., the investigational drug was reduced or discontinued or switched to another drug), their outcome, and date their outcome confirmed in a case report form.

In the event that the physician in charge judged follow-up unnecessary before these symptoms and signs disappear, resolve or return to their baseline status, he/she is to give reasons for such decision in the case report form.

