#### Rationale for the data collection procedures

These procedures were introduced, on the grounds that the incidence of adverse reactions could vary greatly depending on whether it draws on spontaneous reporting by the subjects (passive surveillance) or on interview- or checklist-based reporting by the physicians (active surveillance) for data collection. In the current multi-center trial, safety surveillance data would not be integrated were it not for the procedures for data collection for use by all participating institutions. While data on adverse reactions are usually collected by passive surveillance in studies such as this one, it was decided that active surveillance be employed in this study to collect data on four major symptoms, namely hypoglycemia (particularly in elderly patients), edema, palpitation and shortness of breath to detect signal symptoms of cardiac failure as serious drug-induced adverse reactions, as the study aims to implement rigorous glycemic control and involves the use of thiazolidinedione derivatives.

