### **11.6 Adverse reactions to be anticipated**

All investigators are to refer to the package inserts and the product monographs of the drugs to be used in the trial for information on anticipated adverse reactions with the drugs as well as their rate of occurrence.

Specifically, anticipated adverse reactions include hypoglycemia, edema, cardiac failure, gastrointestinal symptoms including nausea/vomiting and discomfort, anemia, palpitation, skin rash, eczema, high CPK values, rhabdomyolysis, lactic acidosis, leucopenia, thrombocytopenia, hyperkalemia, and abnormal GOT/GPT values.

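### The active symptom checklist leaves out symptoms of low blood pressure, so non-serious episodes are likely under-recorded and the arm comparison loses sensitivity, with bias of uncertain direction

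*Protocol*

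**What the plan says.** Section 11.2 sets out three ways of collecting adverse reactions.

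- Procedure 1 is an open question at interview: physicians are to "encourage them to report spontaneously on any adverse reactions by asking questions".
- Procedure 2 is active checking by interview and checklist, with a stated restriction: "Limit the symptoms to be verified here to the following four symptoms: hypoglycemia, edema, palpitation, and shortness of breath".
- Procedure 3 covers findings that the subject does not perceive: "Additionally, identify changes in the laboratory and vital signs data that may be clinically significant or meaningful". What counts as meaningful is left to the physician.

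The rationale that follows says that "the incidence of adverse reactions could vary greatly depending on whether it draws on spontaneous reporting by the subjects (passive surveillance" or on interview and checklist. It justifies the four symptoms "as the study aims to implement rigorous glycemic control and involves the use of thiazolidinedione derivatives". It does not mention blood pressure.

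Blood pressure is nevertheless one of the three drug-treated factors, and the arms differ in it. The goal is "systolic blood pressure < 120 mmHg and diastolic blood pressure < 75 mmHg" in the intensive arm (section 8.3.1) and "systolic blood pressure < 130 mmHg and diastolic blood pressure < 80 mmHg" in the conventional arm (section 8.3.2). The intensive steps can bring in five antihypertensive classes: ARB or ACE inhibitor, long-acting CCB, diuretic, beta blocker and alpha blocker.

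Section 11.6 refers investigators to package inserts and then names examples, beginning "Specifically, anticipated adverse reactions include hypoglycemia, edema, cardiac failure, gastrointestinal symptoms including nausea/vomiting and discomfort, anemia, palpitation, skin rash". Hypotension, dizziness and syncope are not among the named items. Section 12.3.3 compares adverse-reaction percentages between arms by Fisher's exact test, with a 95% confidence interval for the difference.

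**The concern.** The protocol argues that the way symptoms are collected can change the measured incidence greatly. It then applies active checking to the glycemic and heart-failure symptoms but not to symptoms of its own lower blood pressure goal. This is an explicit limit written into the protocol, not a detail left open for another document.

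Section 12.1 allows the trial to conclude in favor of intensive therapy as a whole. If the symptomatic harm of the blood pressure component is recorded less completely than the glycemic harm, the benefit-harm statement is weakest for that component, and the safety comparison has less chance of showing a difference that exists.

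**Working it through.** The protocol gives no expected rate of hypotension, no capture fraction and no power for the safety comparison, so there is no figure to reproduce. The check has two parts.

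**1. Which route would record a symptom of low blood pressure?**

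| Route | Covers | Leaves out |
|---|---|---|
| Procedure 1, open question | Anything the patient mentions | What the patient does not mention |
| Procedure 2, checklist | The four named symptoms | Dizziness on standing, syncope, falls |
| Procedure 3, vital signs | Readings the physician finds meaningful | Episodes without a low reading; no threshold is given |
| Visit blood pressure, section 9.3 (both arms) | A low value at the visit | Episodes between visits |
| Home readings, section 8.3.1 (recording duty written for the intensive arm) | Low home values in that arm | The conventional arm, for which section 8.3.2 states no such duty |
| Serious reactions, sections 11.4.1 and 11.4.2 | For example, hospitalized cases, whatever the cause, within 72 hours | Non-serious cases |

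What remains is the non-serious episode that the patient perceives and that does not appear as a low reading. It depends on Procedure 1.

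**2. What does incomplete capture do to the comparison?**

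Inputs: 1,271 patients per arm (section 6.2) and a two-sided 5% level. True rates p and capture fractions c are assumptions.

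- Recorded rate in an arm = p × c.
- Recorded difference = pI·cI − pC·cC, with I for intensive and C for conventional.
- Recorded ratio = (pI/pC) × (cI/cC). With equal capture it does not change.
- Approximate power = Φ[(d − 1.96·SE0)/SE1], where d is the recorded difference and SE0 and SE1 are the pooled and unpooled standard errors.

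Worked case, 4% versus 2%, full capture:

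- SE0 = √(0.03 × 0.97 × 2/1271) = 0.00677
- SE1 = √[(0.02 × 0.98 + 0.04 × 0.96)/1271] = 0.00676
- Power = Φ[(0.02 − 1.96 × 0.00677)/0.00676] = Φ(1.00) = 84%

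Equal capture, 4% versus 2%:

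| Capture | Recorded rates | Difference (points) | Ratio | Power |
|---|---|---|---|---|
| 100% | 4.0% v 2.0% | 2.0 | 2.0 | 84% |
| 70% | 2.8% v 1.4% | 1.4 | 2.0 | 69% |
| 50% | 2.0% v 1.0% | 1.0 | 2.0 | 55% |
| 30% | 1.2% v 0.6% | 0.6 | 2.0 | 36% |

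As capture falls from 100% to 30%, power falls from 55% to 20% for 2% versus 1%, and from 87% to 38% for 8% versus 5%. A simulation of the planned Fisher test for 4% versus 2% gave 49% at 50% capture, somewhat below the approximation.

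Unequal capture, better in the intensive arm, 4% versus 2%:

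| Capture I / C | Recorded rates | Difference (points) | Ratio |
|---|---|---|---|
| 60% / 30% | 2.4% v 0.6% | 1.8 | 4.0 |
| 70% / 50% | 2.8% v 1.0% | 1.8 | 2.8 |
| 80% / 50% | 3.2% v 1.0% | 2.2 | 3.2 |

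The difference is overstated once fewer cases are missed in the intensive arm than in the conventional arm, that is when pI(1 − cI) < pC(1 − cC). With cC = 50%, 4%(1 − cI) < 1%, so cI must exceed 75%. The ratio is overstated whenever cI exceeds cC. Power is not shown for these rows, because part of any rejection would come from ascertainment and not from treatment.

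**The case against.** A reader might infer that symptomatic hypotension is left entirely to spontaneous report and that the safety comparison will understate it. The documents support neither statement. Procedure 3, visit blood pressures in both arms, home readings in the intensive arm and serious-reaction reporting all catch part of this harm. The direction of bias is also open. The trial is open-label, and both the home-reading duty (section 8.3.1) and the visit-frequency note (section 8.2.1, Note 1) are written for the intensive arm. Capture may be better there, which could overstate the contrast.

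Other points in the protocol's favor are fair. The four symptoms were chosen for a stated reason. The rationale describes passive collection as usual in such studies and does not call it unreliable. The list in section 11.6 is not exhaustive and points to package inserts, so absence from it does not make hypotension unanticipated. There is no internal contradiction.

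A change would also come late. Enrolment is complete (section 13), and the blood pressure goal was to be reached in 3 to 6 months (section 8.3.1), so much of the titration is likely past.

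What stands after this is narrower: a restriction that ignores one treated factor, and a class of non-serious symptoms with no active route of capture.

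**Conclusion.** The point holds in a limited form. Non-serious symptoms of low blood pressure without a low reading rest on the open question alone. By the protocol's own argument about collection mode, they are likely under-recorded. The section 12.3.3 comparison then loses sensitivity, and the direction of any bias between arms cannot be told from the documents. Equal under-capture shrinks the risk difference, which is the measure the protocol reports, but leaves the ratio unchanged. Better capture in the intensive arm inflates the ratio and can inflate the difference.

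The size is illustrative only. At an assumed 4% versus 2%, equal capture of 50% halves the difference and takes power from 84% to 55%, while 80% versus 50% capture turns 2.0 points into 2.2. All rates and capture fractions are assumed. This is a gap left by a reasoned choice, worth closing because the remedy is small. It does not invalidate the safety analysis.

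**What to change.** In section 11.2, Procedure 2, extend the checklist with dizziness or light-headedness on standing, syncope and falls, asked in the same words and on the same occasions in both arms. Identical questioning addresses both the low capture and the possible imbalance between arms. Name hypotension in section 11.6. Extend the rationale so that it also covers the blood pressure goal. No target, dose or treatment rule changes.

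Compare arms on the added items only for the period after the change, and report that comparison separately from the earlier passively collected data, so that two collection modes are not mixed in one percentage.

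The cost is about three checklist lines and a minor amendment. Section 9.7 already foresees collecting further clinical information by questionnaire when adverse drug reactions need assessment. The limitation is that only the remaining follow-up benefits, so the full-trial power figures above do not describe what the change would deliver.

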#### Procedure 3:

Identify symptoms not perceived by the subjects by auscultation and percussion. Additionally, identify changes in the laboratory and vital signs data that may be clinically significant or meaningful. The physician in charge may use his/her judgment in deciding which change (e.g., in laboratory findings) may be construed as “clinically meaningful”.

The physician in charge is to handle symptoms and signs that newly occurred or worsened after the start of the study as adverse reactions, of all symptoms, signs and changes in laboratory findings, and to deal with them appropriately, to follow up on these symptoms and signs until they disappear, resolve or return to their baseline status, and to describe the name(s) of the adverse reaction(s), date of their occurrence, their extent, their causal relationship to the investigational treatment, their severity, and how they were dealt with (e.g., the investigational drug was reduced or discontinued or switched to another drug), their outcome, and date their outcome confirmed in a case report form.

In the event that the physician in charge judged follow-up unnecessary before these symptoms and signs disappear, resolve or return to their baseline status, he/she is to give reasons for such decision in the case report form.

#### Rationale for the data collection procedures

These procedures were introduced, on the grounds that the incidence of adverse reactions could vary greatly depending on whether it draws on spontaneous reporting by the subjects (passive surveillance) or on interview- or checklist-based reporting by the physicians (active surveillance) for data collection. In the current multi-center trial, safety surveillance data would not be integrated were it not for the procedures for data collection for use by all participating institutions. While data on adverse reactions are usually collected by passive surveillance in studies such as this one, it was decided that active surveillance be employed in this study to collect data on four major symptoms, namely hypoglycemia (particularly in elderly patients), edema, palpitation and shortness of breath to detect signal symptoms of cardiac failure as serious drug-induced adverse reactions, as the study aims to implement rigorous glycemic control and involves the use of thiazolidinedione derivatives.

**11.3 Severity of adverse reactions and their causal relationship to the investigational treatment**

If an adverse reaction occurs, the physician in charge is to rate its severity by using the following three-grade criteria.

|          |                                                                                                                                                                                                                                      |
|----------|--------------------------------------------------------------------------------------------------------------------------------------------------------------------------------------------------------------------------------------|
| Mild     | Symptoms or signs are present but the subject experiencing them does not require treatment to continue with the study                                                                                                                |
| Moderate | Symptoms or signs are present but the subject experiencing them calls also for dose reduction of the investigational drug or addition of another drug to continue with the study                                                     |
| Severe   | The subject experiencing the symptoms and signs is having difficulty performing daily activities, or his/her clinical course is seriously affected by the symptoms and signs, and the investigational drug needs to be discontinued. |

Then, the physician in charge is to rate the casual relationship of the adverse reaction to the investigational drug by using the following four-grade criteria. When the physician in charge judged it to be "unrelated", he/she is to describe the reasons for such judgment.

|                    |                                                                                                                                                                                                                                                                                                                                              |
|--------------------|----------------------------------------------------------------------------------------------------------------------------------------------------------------------------------------------------------------------------------------------------------------------------------------------------------------------------------------------|
| Unrelated          | The adverse reaction can be clearly accounted for by other factors than the investigational drug.                                                                                                                                                                                                                                            |
| Possibly related   | While the adverse reaction is assumed to have resulted from other factors than the investigational drug, its causal relationship cannot entirely be ruled out.                                                                                                                                                                               |
| Probably related   | The adverse reaction is least likely to have resulted from other factors than the investigational drug.                                                                                                                                                                                                                                      |
| Definitely related | The adverse reaction is highly likely to have resulted from the investigational drug, e.g., there is a time-dependent association between the time the investigational drug was given and the occurrence of the adverse reaction, or the adverse reaction cannot be accounted for by other reasons than the use of the investigational drug. |

All adverse reactions except those defined as "unrelated" are to be handled as side effects.

**11.4 Serious adverse reactions****11.4.1 Technical terminology**

Any adverse reaction is defined as serious adverse reactions, if it:

|                                                                                                                                                                                                                                |
|--------------------------------------------------------------------------------------------------------------------------------------------------------------------------------------------------------------------------------|
| Is fatal                                                                                                                                                                                                                       |
| Is life-threatening                                                                                                                                                                                                            |
| Leads to the subject becoming hospitalized or calling for prolonged hospitalization or treatment                                                                                                                               |
| Leads to permanent or serious damage or dysfunction in the subject                                                                                                                                                             |
| Causes congenital anomaly                                                                                                                                                                                                      |
| Is serious hypoglycemia accompanied by impaired consciousness                                                                                                                                                                  |
| Is some other serious medical phenomenon                                                                                                                                                                                       |
| Or is serious enough to place the subject in a critical situation calling for treatment to avoid the outcomes described above, while it is not immediately fatal, life-threatening or leads to the subject being hospitalized. |

**11.4.2 Reporting procedure**

When a serious adverse reaction occurred, irrespective of its causal relationship to the investigational drug, the physician in charge is to report the adverse reaction to the Trial Secretariat Office within 72 hours of his/her knowledge of its occurrence.

In this regard, the deadline for reporting to the supervisor at his/her own healthcare institution is to be consistent with the regulations laid down by the institution for such reporting. Similarly, all participating healthcare institutions are to report spontaneously to the Pharmaceutical and Food Safety Bureau, Ministry of Health, Labor and Welfare (MHLW), in accordance with the MHLW undertaking, the "Pharmaceuticals and Medical Device Safety Information Reporting System", as well as to relevant pharmaceutical companies in accordance with the "Pharma Reporting System" based on the Pharmaceutical Affairs Law.

